### Measures

#### Primary Outcome

The primary endpoint is the anxiety-related part of the CINT questionnaire on the experiences and the emotional state in the ICU which is being recorded at the time of admission to the standard ward. This questionnaire has already been used in preliminary studies [20,22] and represents specific aspects of the quality of life in relation to the ICU. The anxiety-related part corresponds to the experienced anxieties during the ICU stay and comprehends the following items: death related fear, fear of severe suffering, fear of a handicap, fear of the future, fear of uncertainty, panic, strain, depression, loneliness, melancholy, lack of orientation, uncertainty, anger optimism and confidence. All items are rated on a 4-point Likert-scale from "never" to "always" (see Figure 2).

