### Inclusion and exclusion criteria

Cardiac surgery, general surgery and internist patients with scheduled and unscheduled ICU stay (including High Dependency Units) will be eligible for inclusion in this trial. Exclusion criteria, besides a refusal to take part in the trial, are: no opportunity to fill in the mailed follow-up questionnaire, impaired cognitive ability and/or ability of judgment, language problems, accommodation in one room with another study patient, or age under 18 years.

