#### Secondary Outcomes

In addition to the anxiety-related part of the CINT questionnaire a Visual Analogue Scale-Anxiety - VAS-A [27] supported by the Faces Anxiety Scale [28] is used. Evaluation of potential discrepancies between the retrospectively reported anxiety and the measured anxiety during the ICU-stay is of particular interest. The State and Trait Anxiety Inventory - STAI [29] as a further anxiety-related instrument will be recorded to compare anxiety after ICU-stay.

Furthermore the CINT questionnaire [20,22] measures additional parameters of the ICU related experiences.

As a secondary variable, the patients' level of consciousness and concentration regarding a potential ICU-caused state of confusion will be surveyed with the Confusion Assessment Method for the ICU - CAM-ICU [25,26]. The test procedure CAM-ICU, also appropriate for ventilated patients, comprehends cognitive as well as process-related components. These components are illustrated using the Richmond Agitation and Sedation Scale - RASS [24] and the four delirium main criteria "acute onset", "inattention", "disorganized thinking" and "altered level of consciousness".

For the analysis of additional effects the duration of stays (ICU, intermediate care, standard ward, hospital) and routine date on the course of inpatient treatment are recorded. Socio-demographic data like age, gender, marital status and routine treatment data like medical diagnoses will be documented thoroughly.

Uncertainty tolerance will be measured using the Uncertainty Tolerance Scale [30] and semi-structured questions on convalescence are asked to get a qualitative impression of the participants health state.

Expected results will contribute to an improved communication in the ICU and finally to an improved quality of life as a desired treatment goal [31-33]. Therefore we will measure quality of life using the Schedule for Evaluation of Individual Quality of Life - SEIQoL [34], and the SF-12 [35]. For this reason we implemented a paper questionnaire version of the SEIQoL to test for acceptance of a self evaluation form for this kind of quality of life questionnaire.

All measurements and the timeline are summarized in Table 2.

**Table 2 T2:** Measurements.

t_0_	day of recruitment (ICU)	▪ Socio-demographic data, routine treatment data^2^ ▪ Acute ICU-Syndrome (CAM-ICU incl. RASS)^2^ ▪ Anxiety (VAS-A)^1^
t_1_	24 h after study intervention	▪ Acute ICU-Syndrome (CAM-ICU incl. RASS)^2^ ▪ Anxiety (VAS-A)^1^

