t_2_	48 h after study intervention	▪ Acute ICU-Syndrome (CAM-ICU incl. RASS)^2^ ▪ Anxiety (VAS-A)^1^

t_3_	admission to standard ward	▪ Experience and emotional state in the ICU (CINT-FB)^1^ ▪ Anxiety (VAS-A)^1^ ▪ State-Anxiety (STAI-State)^1^ Estimated time for the questionnaire: 20 minutes

t_4_	discharge from hospital	▪ In-patient history and postoperative complications^2^ ▪ Length of stay and mode of discharge^2^

t_5_	3 months after discharge (by mail)	▪ Individual quality of life (SEIQoL)^1^ ▪ Quality of life (SF - 12)^1^ ▪ Uncertainty (Uncertainty Tolerance Scale)^1^ ▪ Convalescence (Semi-structured questions)^1^ ▪ Trait-Anxiety (STAI-Trait)^1^ Estimated time for the questionnaire: 15 minutes

Points of measurement and outcome measures according to case report form.

^1^Self evaluation; ^2 ^Third-party evaluation

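### The primary anxiety score is collected only on arrival at a standard ward, so a survivor who leaves the hospital's critical-care units by another route loses the only primary measurement

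*Protocol article*

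**What the plan says.** All references are to the protocol article.

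- **Primary Outcome:** the endpoint is the anxiety-related part of the CINT, covering experiences and "the emotional state in the ICU which is being recorded at the time of admission to the standard ward". It is retrospective: "The anxiety-related part corresponds to the experienced anxieties during the ICU stay".
- **Table 2 (Secondary Outcomes):** t3 is labelled "admission to standard ward" and is the only row with the CINT. It also carries VAS-A and STAI-State. No time window is given.
- **Table 2, other rows:** t0 to t2 carry CAM-ICU with RASS, and VAS-A (t0 also baseline data). t4, at hospital discharge, is third-party data only and includes "Length of stay and mode of discharge". t5 is a mailing with other instruments.
- **Inclusion and exclusion criteria:** "patients with scheduled and unscheduled ICU stay (including High Dependency Units) will be eligible for inclusion in this trial".
- **Intermediate care as a separate step:** the Secondary Outcomes section lists its duration apart from ICU and standard ward, and topic 5 of Table 1 explains the transfer to it.
- **Drop-outs and Data analysis:** drop-outs contribute data up to the time they drop out, and intention to treat is declared for all outcomes.

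**The concern.** The endpoint asks about the ICU stay, but its collection depends on reaching a later place. The plan enrols scheduled and unscheduled ICU and HDU patients and records how each was discharged, so it expects routes to differ. It gives no instruction for a survivor whose route does not include a standard ward.

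Such a patient is alive and may be able to answer, yet no visit asks for the CINT. Counting drop-outs up to their exit does not help, because no primary value exists before t3. Intention to treat is declared, but the primary comparison would in practice cover only those who reached a ward. Whether a patient gets there is settled after randomisation by clinical course, so the loss need not be random.

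A smaller matter goes with it. A patient who passes through intermediate care is asked about the ICU after an interval that the plan does not fix, and Table 2 does not list the CINT completion date among the recorded items.

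**Working it through.** **1. Is there any second chance to collect the CINT?**

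| Visit | Timing | CINT? |
|---|---|---|
| t0 | recruitment, in the ICU | no |
| t1, t2 | 24 h and 48 h after the intervention | no |
| t3 | arrival on the standard ward | yes |
| t4 | hospital discharge | no (third-party data) |
| t5 | three months, by mail | no (other instruments) |

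No route that omits the ward produces a primary value.

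**2. The plan's own sample size.** Inputs from Sample size calculation: Δ = 8.5, SD = 17, α = 0.05 (two-sided assumed, as the article does not say), power 0.80.

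n per group = 2 × (1.96 + 0.842)² × (17/8.5)² = 2 × 7.85 × 4 = 62.8, so 63 (64 with the t-test). The stated minimum of 70 is not reproduced but errs on the safe side. The reserve is (100 − 70)/100 = 30%, or 200 − 2 × 70 = 60 patients.

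**3. Does missing t3 data threaten power?** With a share m of each arm missing for any reason, n = 100(1 − m), and power = Φ(0.5 × √(n/2) − 1.96):

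| m | n per arm | Power |
|---|---|---|
| 10% | 90 | 91.8% |
| 15% | 85 | 0.5 × √42.5 = 3.26; 3.26 − 1.96 = 1.30; 90% |
| 20% | 80 | 88.5% |
| 30% | 70 | 84.1% |
| 37% | 63 | 80.1% |
| 40% | 60 | 78.2% |

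Power stays at or above 80% until about 36–37% are missing.

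**4. How many patients?** The article gives no share. Each 1% of the sample is 2 of 200 patients. As an assumption only, 5% to 15% would be 10 to 30 patients. These are upper figures for that range, since deaths are not taken out first.

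**5. What could the loss do to the estimate?** In one arm let m now be the share of survivors who bypass the ward, and d the mean score of those who reach the ward minus that of those who do not. The mean of all survivors is (1 − m) × (mean, ward) + m × (mean, bypass), so the observed mean differs from it by m × d. The treatment difference is therefore shifted by

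m(intervention) × d(intervention) − m(control) × d(control).

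This is zero if m and d are the same in both arms. As an illustration on assumed values, m = 15% against 5% with |d| = 17 (one SD) in both arms gives 0.10 × 17 = 1.7 points, or 1.7/8.5 = 20% of Δ. Nothing in the article says that m or d differs by arm, so this shows scale and is not an estimate.

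**The case against.** **An article condenses a fuller protocol.** Table 2 refers to the case report form, and the Quality assessment section says that procedures were documented jointly across centers. A fallback may exist there. That is fair, and if it does, the remedy is to state it. But the time at which the primary endpoint is taken belongs to its definition. The article fixes it in two places, consistently and without exception.

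**Power and balance.** The reserve absorbs a plausible loss. Randomisation is stratified by center and unit, center is in the primary ANCOVA, and a conversation of about ten minutes may well not change the route out of the ICU. This stands. A reader might infer that the trial is underpowered or the treatment effect biased, and the documents support neither.

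**Recall delay.** A reader might also infer that t3 is wrongly anchored for everyone and should become a window after ICU/HDU exit. The documents do not support that either:

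- They give no length of intermediate-care stay, so a delay of days is not established.
- The questionnaire refers to the ICU stay, so contamination by intermediate-care experience is conjecture.
- They do not say whether HDU and IMC overlap.
- Ward admission gives all assessed patients a common setting, which matters because VAS-A and STAI-State are taken at the same visit.

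Equal delay against equal setting is a trade-off, and the plan's choice is defensible. The duration of intermediate care and the mode of discharge are already recorded, so part of the description is possible.

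**Deaths before ward admission** remain without a score whatever is done. The point concerns survivors only.

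**Conclusion.** The point holds in a limited form. Under the stated rule, a survivor who bypasses the standard ward has no primary value and no later visit recovers it. This follows from the Primary Outcome text and Table 2 without any assumption. The number affected is unknown; the 10 to 30 patients above rest on an assumed 5% to 15%.

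What is at stake is primary data that could have been obtained, with loss tied to clinical course after randomisation. A larger sample does not repair that kind of loss. The varying recall interval after intermediate care is a matter for description or a sensitivity analysis. The change is worth making because it is nearly free and alters which data are collected.

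**What to change.** Keep admission to the standard ward as the usual t3. Add to the Primary Outcome section and to the t3 row of Table 2, for example:

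*A patient who leaves the ICU, HDU or intermediate care without a stay on a standard ward completes the t3 questionnaires (CINT, VAS-A, STAI-State) before departure. The dates of ICU/HDU exit and of CINT completion are recorded.*

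The rule works whether or not HDU and intermediate care overlap. The two dates allow the recall interval to be described by arm and, if wanted, examined in a sensitivity analysis. The primary model need not change.

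Cost: a short addition to the text, Table 2 and the case report form, and an amendment to the ethics committees if recruitment has begun. No patient gets an additional visit. The downside is small: a few questionnaires are completed away from the ward, and staff must learn of a departure in time.

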**Figure 2 F2:**
[figure not shown]
**Measurement of anxieties during the ICU stay**. Anxiety-related part of the CINT questionnaire (translated version).

#### Secondary Outcomes

In addition to the anxiety-related part of the CINT questionnaire a Visual Analogue Scale-Anxiety - VAS-A [27] supported by the Faces Anxiety Scale [28] is used. Evaluation of potential discrepancies between the retrospectively reported anxiety and the measured anxiety during the ICU-stay is of particular interest. The State and Trait Anxiety Inventory - STAI [29] as a further anxiety-related instrument will be recorded to compare anxiety after ICU-stay.

Furthermore the CINT questionnaire [20,22] measures additional parameters of the ICU related experiences.

As a secondary variable, the patients' level of consciousness and concentration regarding a potential ICU-caused state of confusion will be surveyed with the Confusion Assessment Method for the ICU - CAM-ICU [25,26]. The test procedure CAM-ICU, also appropriate for ventilated patients, comprehends cognitive as well as process-related components. These components are illustrated using the Richmond Agitation and Sedation Scale - RASS [24] and the four delirium main criteria "acute onset", "inattention", "disorganized thinking" and "altered level of consciousness".

For the analysis of additional effects the duration of stays (ICU, intermediate care, standard ward, hospital) and routine date on the course of inpatient treatment are recorded. Socio-demographic data like age, gender, marital status and routine treatment data like medical diagnoses will be documented thoroughly.

Uncertainty tolerance will be measured using the Uncertainty Tolerance Scale [30] and semi-structured questions on convalescence are asked to get a qualitative impression of the participants health state.

Expected results will contribute to an improved communication in the ICU and finally to an improved quality of life as a desired treatment goal [31-33]. Therefore we will measure quality of life using the Schedule for Evaluation of Individual Quality of Life - SEIQoL [34], and the SF-12 [35]. For this reason we implemented a paper questionnaire version of the SEIQoL to test for acceptance of a self evaluation form for this kind of quality of life questionnaire.

All measurements and the timeline are summarized in Table 2.

**Table 2 T2:** Measurements.

t_0_	day of recruitment (ICU)	▪ Socio-demographic data, routine treatment data^2^ ▪ Acute ICU-Syndrome (CAM-ICU incl. RASS)^2^ ▪ Anxiety (VAS-A)^1^
t_1_	24 h after study intervention	▪ Acute ICU-Syndrome (CAM-ICU incl. RASS)^2^ ▪ Anxiety (VAS-A)^1^

t_2_	48 h after study intervention	▪ Acute ICU-Syndrome (CAM-ICU incl. RASS)^2^ ▪ Anxiety (VAS-A)^1^

t_3_	admission to standard ward	▪ Experience and emotional state in the ICU (CINT-FB)^1^ ▪ Anxiety (VAS-A)^1^ ▪ State-Anxiety (STAI-State)^1^ Estimated time for the questionnaire: 20 minutes

t_4_	discharge from hospital	▪ In-patient history and postoperative complications^2^ ▪ Length of stay and mode of discharge^2^

t_5_	3 months after discharge (by mail)	▪ Individual quality of life (SEIQoL)^1^ ▪ Quality of life (SF - 12)^1^ ▪ Uncertainty (Uncertainty Tolerance Scale)^1^ ▪ Convalescence (Semi-structured questions)^1^ ▪ Trait-Anxiety (STAI-Trait)^1^ Estimated time for the questionnaire: 15 minutes

Points of measurement and outcome measures according to case report form.

^1^Self evaluation; ^2 ^Third-party evaluation

### Sample size calculation

The sample size calculation is based on the anxiety-related part of the CINT questionnaire as particular aspects of the ICU-patients' quality of life [21]. This sum score can be represented on a scale from 0 to 100 and has added up to a mean value of M = 28.0 and a standard deviation of SD = 17.0 in an earlier unpublished trial. The basis for the sample size calculation was formed by the following assumptions: α = 0.05; β = 0.20; Δ = 8.50 scale points. The determination of the expected difference Δ was done on the notion that in quality of life measures the differences within the scope of half a standard deviation are considered as minimally clinically relevant [36]. Under these conditions at least 70 patients per group have to be included to ensure the effect statistically. In order to compensate potential drop-outs the sample size was determined n = 100 per group, corresponding to a total sample size of N = 200 (n = 100 vs. n = 100). In the centers Stuttgart and Halle respectively n = 30 patients per study group will be recruited, in Marburg n = 40 per study group.

### Drop-outs

Drop-outs will be documented thoroughly and included in the data analysis until the point of drop-out. Reasons for drop-out will be reported and analyzed.

### Data analysis

Descriptive analyses will be carried out by standard methods, taking into consideration the scale of the respective variables. For analysis of the primary endpoint we will use an ANCOVA model with the primary endpoint as the response, and the center as a covariate, thus allowing for the stratified randomization procedure. The treatment effect will be reported as an adjusted difference in means with a corresponding 95% confidence interval. Secondary endpoints will be assessed with the respective adjusted models, using standard ANCOVA models for continuous outcomes and logistic regression for binary outcomes. In case of repeatedly measured outcomes, mixed models will be used for analyses to adjust for within-patient correlations [37]. Secondary endpoints analyses are considered as merely exploratory. The analysis of all outcomes will obey to the intention-to-treat principle. Subgroup analyses will be conducted as interaction tests, also in a non-confirmatory fashion [38].

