**Figure 1 F1:**
[figure not shown]
**Obtaining patient consent**. Patient information leaflet and patient consent form (translated version).

All patients who are to be admitted electively to the ICU will be informed about the possibility of taking part in the trial before the transfer to the ICU or before the surgery and their informed consent will be obtained. This applies to the major part of cardiac surgery patients as well as to a minor part of the general surgery patients. All other patients, particularly those of internal medicine and trauma surgery, will be informed about the trial in the early stages of their intensive care stay and will be asked to take part. In case custodians are appointed, they will be informed about the possibility of taking part in the trial and will be asked for a participation of their charge in the trial.

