### Randomization

The group allocation is done via concealed randomization (concealed allocation) on the patient level, stratified by center and unit into 2 study groups:

▪ structured information at the beginning of the ICU stay (*Intervention group*) or

▪ sham comparator, unspecific conversation (*Control group*).

The randomization list will be computer-generated before the start of the trial (Institute of Medical Epidemiology, Biostatistics, and Informatics, Halle/Saale). Concealed randomization will be realized by using opaque, consecutively numbered envelopes after the inclusion of the study patients.

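### The primary ANCOVA adjusts for center only: adding unit (a stratification factor) and the already collected t0 VAS-A would be a free improvement to a valid analysis

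*Protocol article*

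**What the plan says.** The Data analysis section writes the primary model out as an "ANCOVA model with the primary endpoint as the response, and the center as a covariate", and presents the center term as the allowance for the stratified randomization. No other covariate is named for the primary endpoint.

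The Randomization section describes allocation as "stratified by center and unit into 2 study groups", so there are two stratification factors and the model carries one.

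The primary endpoint is the anxiety-related part of the CINT questionnaire, "which is being recorded at the time of admission to the standard ward" (Primary Outcome). It "corresponds to the experienced anxieties during the ICU stay", so it looks back over the stay and cannot have a baseline value of its own.

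Table 2 lists a self-rated VAS-A at t0, t1, t2 and t3. It labels t0 "day of recruitment (ICU") and puts t1 at 24 h after the study intervention. The t0 VAS-A is thus the only early anxiety rating in the schedule.

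Eligible are "patients with scheduled and unscheduled ICU stay (including High Dependency Units"), from cardiac surgery, general surgery and internal medicine.

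**The concern.** The endpoint is an anxiety score, the patients differ widely in how they reach the ICU, and an anxiety rating is scheduled at baseline. A model that ignores this rating leaves explainable variance in the residual. It also leaves any chance difference in initial anxiety between the arms in the treatment estimate. Stratification by unit restrains imbalance in case mix, and so partly in elective status, but not in anxiety among patients of the same unit.

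The sentence is also at odds with the Randomization section. It presents the center term as what accounts for the stratification, but unit was a stratification factor too. If units differ in mean anxiety and stratification has balanced them, leaving unit out keeps between-unit variance in the residual and makes the reported confidence interval wider than it need be.

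The stakes are the width of the interval and the credibility of the estimate if the arms happen to differ at t0. Adding baseline anxiety only after such a difference is seen would invite the charge of a data-driven model, so the choice belongs in the plan.

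**Working it through.** **Inputs from the article (Sample size calculation).** SD = 17.0, difference 8.5 points, α = 0.05 (two-sided assumed, as sidedness is not stated), β = 0.20, 70 per group needed, 100 per group recruited.

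**Input not in the article.** The correlation r between t0 VAS-A and the CINT anxiety score. It is an assumption here, shown from 0 to 0.5.

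**The plan's own figure.** n per group = 2(1.96 + 0.842)² × (17/8.5)² = 62.8, so 63 by the normal approximation and 64 by the t-test. The stated 70 is not reproduced exactly, but it errs on the safe side. The step to 100 equals 70/(1 − 0.30).

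**Power of the planned model at 70 per group.**
- SE of the difference = 17 × √(2/70) = 2.87.
- Normal approximation: Φ(8.5/2.87 − 1.96) = 84.1%. The t-test gives 83.6%.
- At 100 per group, power is about 94%.

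The planned 80% is therefore met without any baseline covariate.

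**Effect of adding t0 VAS-A.** Residual SD = 17 × √(1 − r²). Half-width = 1.96 × residual SD × √(2/70). Power is from the two-sample t-test with that SD; the few degrees of freedom spent on covariates are ignored.

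| r (assumed) | Variance removed (r²) | Residual SD | Power, 70 per group | 95% CI half-width |
|---|---|---|---|---|
| 0 | 0% | 17.00 | 83.6% | 5.63 |
| 0.2 | 4% | 16.66 | 85.0% | 5.52 |
| 0.3 | 9% | 16.22 | 86.8% | 5.37 |
| 0.4 | 16% | 15.58 | 89.3% | 5.16 |
| 0.5 | 25% | 14.72 | 92.4% | 4.88 |

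**Chance imbalance.** If the arms differ at t0 by k standard errors of the baseline difference, the unadjusted estimate is expected to shift by k × r × 17 × √(2/70).
- k = 1: 0.6 points at r = 0.2, 0.9 at r = 0.3, 1.4 at r = 0.5.
- k = 1.96: 1.1, 1.7 and 2.8 points, against the target of 8.5.

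**Missing t0 ratings.** With a fraction m missing, and mean imputation plus an indicator, the variance removed falls to roughly (1 − m)r². As an illustration, m = 0.3 and r = 0.5 give 0.7 × 0.25 = 17.5%, and a half-width of 5.63 × √0.825 = 5.1 instead of 4.9.

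**Unit.** The article gives no between-unit variance, so the gain from adding unit cannot be sized. This part rests on comparing the two sections: two factors in the randomization, one in the model.

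**Timing of t0.** Three places bear on it.
- Recruitment of participants: elective patients "will be informed about the possibility of taking part in the trial before the transfer to the ICU or before the surgery", and consent is obtained then.
- Table 2: t0 is placed in the ICU and pairs VAS-A with CAM-ICU and RASS.
- Study procedure: CAM-ICU and RASS are recorded before the conversation; VAS-A is not mentioned there.

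The natural reading is an ICU baseline before the conversation. The wording does not say so for VAS-A, and nothing places the rating before the allocation envelope is opened.

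**The case against.** **Nothing here is invalid.** Under randomization, the comparison without baseline anxiety is unbiased with valid type I error. The sample size uses the unadjusted SD and reaches its target. All of this stands. A reader might infer that the primary analysis is biased or underpowered; the article's figures do not support that.

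**VAS-A is not a baseline of the endpoint.** CINT is a retrospective multi-item score that also covers items such as loneliness, anger and confidence. VAS-A is a single rating at one moment. The Secondary Outcomes section treats possible disagreement between the two as a question of interest. This stands too. A reader might take a correlation of 0.3 to 0.5 for granted, but the article gives no source for it. At r = 0.2 the gain is only 1.4 points of power (83.6% to 85.0%).

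**The rating may be missing.** It is self-rated, and the conversation is allowed from RASS −3 upward, so gaps at t0 are plausible and would reduce the gain.

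**The t0 timing is not a contradiction.** A reader might infer that elective patients give their t0 rating before surgery. The recruitment text concerns information and consent, while Table 2 places t0 in the ICU. Nor does any text say that VAS-A follows the conversation. What remains is loose wording: for patients who consented earlier, the recruitment day need not be an ICU day.

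**Stratification already helps.** Stratifying by unit limits imbalance in case mix and, in part, in elective status. An elective/non-elective term is therefore optional.

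What survives is that the article writes the model out rather than leaving it open, that the model omits a stratification factor it claims to allow for, and that it leaves unused a measurement already scheduled.

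**Conclusion.** The point holds as a free improvement. The planned primary analysis is valid and exceeds its planned power at 70 per group (about 84% against 80%). It omits unit, contrary to its own rationale, and forgoes the precision and protection that t0 VAS-A could give.

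The size is uncertain: negligible near r = 0, small at r = 0.2 (half-width 5.6 to 5.5 points) and useful at r = 0.5 (4.9 points, power about 92%). These figures assume SD 17.0, a two-sided α of 0.05, 70 evaluable patients per group, a linear relation, and a t0 rating that is complete and taken before allocation is known. The last condition matters because neither patients nor field researchers are blinded. At the recruited 100 per group, power is already about 94%, so the benefit there would mainly be a narrower interval.

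**What to change.** - **Model.** Prespecify the primary ANCOVA as treatment + center + unit + t0 VAS-A (continuous). An elective/non-elective term may be added but is not needed.
- **Timing.** State in Table 2 and in Study procedure that t0 VAS-A is taken in the ICU, before the study conversation and before allocation is revealed, for every patient. This also secures the baseline for the repeated-measures analysis of VAS-A.
- **Missing t0 ratings.** Use mean imputation with a missing indicator, so that no patient leaves the primary analysis.

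The cost is a few degrees of freedom, one rewritten model sentence and one clarified time point. If VAS-A is currently taken after the envelope is opened at any center, the order of two steps changes as well. No new measurement and no additional patients are required.

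### The primary ANCOVA adjusts for center but not unit, so it allows for only one of the two randomization strata (minor; a free improvement)

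*Protocol article*

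**What the plan says.** Two sections of the protocol article bear on this.

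- **Randomization:** allocation is at patient level, "stratified by center and unit into 2 study groups". The list is prepared in advance: "The randomization list will be computer-generated before the start of the trial". Block size and the number of units per center are not given.
- **Data analysis:** the primary endpoint is the response in an ANCOVA with "the center as a covariate, thus allowing for the stratified randomization procedure". The treatment effect is to be reported as an adjusted mean difference with a 95% confidence interval. Unit is not named as a covariate here or anywhere else in the article.

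The article does not define unit. The eligible population is described as "Cardiac surgery, general surgery and internist patients with scheduled and unscheduled ICU stay", with high dependency units included.

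**The concern.** The Data analysis section names a covariate and gives a reason for it, and the reason does not fit the Randomization section: one of the two stratification factors is missing from the model that is said to account for them.

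This can matter because stratified allocation, when it balances the arms within unit, removes most of the between-unit variation from the treatment contrast. A model without unit still counts that variation as residual noise. If unit is prognostic, the model-based standard error then exceeds the real sampling variability of the estimate. The confidence interval covers slightly more than 95%, the test runs below its nominal 5%, and part of the precision that the stratification could deliver is not used.

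It is plausible that unit is prognostic. The section on recruitment says that elective admission applies to most cardiac surgery patients but only a minority of general surgery patients, and that internal medicine and trauma patients in particular are approached once already in intensive care. If units follow specialty, unit tracks planned versus unplanned admission. That the investigators chose to stratify on it suggests that they thought it mattered. The article does not, however, link unit to the anxiety score.

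**Working it through.** **Inputs from the article (Sample size calculation).** "a standard deviation of SD = 17.0 in an earlier unpublished trial"; "α = 0.05; β = 0.20; Δ = 8.50 scale points"; 70 evaluable and 100 recruited per group; centers of 80, 60 and 60 patients in total (40, 30 and 30 per arm).

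**The plan's own figure.** For a two-sided 5% test with 80% power, n per group = 2 × (1.96 + 0.8416)² × 17² / 8.5² = 62.8, so 63 (64 by the t-test). The stated 70 is not reproduced, but it errs on the safe side: 70 per group gives 84.1% power (83.6% by the t-test). The step 70 / (1 − 0.30) = 100 implies a 30% drop-out allowance. With 70 per group, the standard error of the difference is 17 × √(2/70) = 2.87.

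**Assumptions not in the article.** R² is the share of outcome variance that unit explains within center. No figure is given, so it is varied from 0 to 0.30. Also assumed: three equally common units in each center, permuted blocks of 4 within center-by-unit strata, and 30% loss at random. The total SD is held at 17.

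**Upper limit by formula.** With perfect balance within unit among those analyzed, the excess in the standard error is 1/√(1 − R²): 1.026 at R² = 0.05 and 1.054 at 0.10. The type I error is 2 × (1 − Φ(1.96/√(1 − R²))): 4.4% and 3.9%. Drop-out disturbs that balance, so a simulation is the better guide.

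**Simulation under no treatment effect (6000 runs per row).**

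| R² | Model SE, center only | True spread of that estimate | Excess | Type I error, center only | Model SE, center + unit |
|---|---|---|---|---|---|
| 0 | 2.88 | 2.87 | about 0% | 4.8% | 2.89 |
| 0.05 | 2.88 | 2.81 | about 2.5% | 4.4% | 2.81 |
| 0.10 | 2.88 | 2.79 | about 3% | 4.2% | 2.74 |
| 0.20 | 2.88 | 2.68 | about 7% | 3.3% | 2.58 |
| 0.30 | 2.89 | 2.58 | about 12% | 2.4% | 2.42 |

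The Monte Carlo error is about 1 percentage point on the excess (1/√(2 × 6000) = 0.9%) and 0.3 points on the type I error (√(0.05 × 0.95/6000)). A separate run with exactly 140 of 200 retained (8000 runs) gave an excess of about 0%, 2% and 6% at R² = 0.05, 0.10 and 0.15.

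**Power at 8.5 points (3000 runs per row).**

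| R² | Center only | Center + unit |
|---|---|---|
| 0 | 82.7% | 82.7% |
| 0.05 | 83.9% | 85.2% |
| 0.10 | 84.3% | 87.0% |
| 0.20 | 84.0% | 89.9% |
| 0.30 | 85.3% | 93.3% |

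**If the list does not balance within unit** (simple randomization, R² = 0.20), the center-only standard error is about right: 2.90 against a spread of 2.87, type I error 4.6%. Adding unit still lowers the standard error, to 2.62.

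**The case against.** The strongest case on the other side is that little harm follows. Leaving a stratification factor out of a linear model does not bias the treatment difference, and the error here is in the conservative direction. Power with center only stays at 83–85% across the range examined, above the planned 80%, partly because 70 per group is more than the 63–64 required. This stands, and it sets the severity.

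A second objection is that unit is undefined. The three specialties are listed as eligible patient types, not as strata, and where a center contributes a single unit, center already captures it. This also stands: the size of the effect cannot be read from the article. It does not remove the mismatch, because the Randomization section treats unit as a factor in addition to center.

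A third is that covariate detail belongs in an analysis plan that is not shown. That would answer silence, but the article names the covariate and says what it achieves.

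A reader might infer that the primary standard error is definitely too large. The documents do not support that: it needs both a prognostic unit and balance within unit, and they give no figure for either. Nor do they show that the secondary analyses share the omission. Those models are described only as adjusted, without listed covariates, and are exploratory.

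**Conclusion.** The inconsistency is certain: the primary model allows for the stratification by center but not by unit. Its statistical effect is conditional and probably small. If unit predicts the anxiety score within center and the list balances the arms within unit, the center-only standard error is too large by about 2–3% at R² = 0.05–0.10 and 7% at 0.20, with type I error of 4.4–4.2% and 3.3%. The power given up is about 1 to 3 points at R² = 0.05–0.10 and 6 points at 0.20. At R² = 0 nothing is lost. These figures rest on the assumed unit structure, block size and random loss.

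It would be wrong to conclude that the primary test is invalid or the trial underpowered. The estimate is unbiased, the type I error is not inflated, and planned power is kept. This is a minor point and a free improvement.

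**What to change.** In the Data analysis section, specify the primary ANCOVA as treatment, center and unit as categorical factors, or treatment plus the center-by-unit strata. Define unit, and state before the data are seen how sparse units will be pooled. Use the same factors in the exploratory secondary models where numbers allow. If unit is deliberately left out, reword the justification to say that the model allows for stratification by center only.

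The cost is one or two sentences and a few degrees of freedom out of about 140. Unit must already be known in order to randomize, so no data are added. If unit proves not to be prognostic, the price is negligible: a standard error of 2.89 instead of 2.88, with power at 82.7% either way.
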